### Interventions

The intervention group will receive both the typical premarital counselling and a fertility knowledge training containing verbal and virtual educational program at five time episodes (one verbal session and four virtual sessions) in a package. We will implement the educational programs during 4 weeks. The intervention includes a 30-min lecture, documentary videos, text messages and short films. The control group will receive only typical premarital counselling. The content of educational or counselling program will be based on the most updated literature on fertility knowledge.

The educational program was developed based on new guidelines of American Society for Reproductive Medicine (ASRM), European Society of Human Reproduction and Embryology (ESHRE) and Iran’s Ministry of Health and Medical Education (MOHME).

The fertility knowledge package will consist of information on fertility rates, infertility rates, risks of delay in childbearing, safe waiting period for parenting, Impact of age on female fertility, limited fertility period for women, fertility window and how to optimize fertility, impact of weight and lifestyle on fertility, definition of infertility, infertility risk factors, impact of sexually transmitted diseases (STDs) on fertility, the need for earlier evaluation and treatment of infertility, success rate and financial costs of infertility treatments, assisted conception and fertility preservation. In order to incorporate multidisciplinary views in this study, specialists from different relevant disciplines will be invited to provide their views on different stages of the study including the suitability of the educational content. A group of experts composed of midwife, reproductive health professional, gynecologist (infertility fellowship), medical sociologist, health psychologist and health education will evaluate and confirm the scientific validity of the intervention package. The content of educational program will be also assessed in the pilot phase.

Instructors will be trained by the principal investigator before the intervention and their questions will be answered. The educational content will be provided to them as a booklet for future reading. Further, they will be asked to record the educational counselling session as an audio file for evaluation by the principal investigator. In order to increase the quality of the training program, some features will be considered, such as having a long training period (1 month), using the power of media, having intermittent training with reminders and repeating in regular basis, and in this way the triangulation will enhance the quality of the counselling program.

### Outcomes

The primary outcomes are fertility knowledge, childbearing intention and the first planned pregnancy rate (positive pregnancy test).

The secondary outcomes include the contraception method use, miscarriage and unplanned pregnancy.

### Data collection

Data will be collected by questionnaires at baseline and 3, 12 and 18 months after the intervention in each selected city (Table 1). The post-test questionnaires will be completed by the participants through online forms. The participants’ phone number, email address and social network’s ID (WhatsApp) will be asked in order to send the post-test questionnaire links and some virtual educational materials.

In each city, two research collaborators will cooperate with the principal investigator. They will be introduced by the Ministry of Health and Medical Education, associated office for premarital counselling courses in all provinces. We will have a training session for these research staff and they will be justified about the study aims and procedure of data collection as well as educational intervention. They need to be in close contract with the principal investigator.

To minimize loss to follow up, we will provide an incentive to the eligible participants (A gift voucher for free sexual and reproductive health counselling) on the completion of the survey which may increase response rates. Four reminder emails or text messages will send out to non-respondents at one, two, three, and 4 weeks; a fifth telephone reminder was also undertaken.

Since a recent study in Iran showed an average interval between marriage and first pregnancy as about 15.4 ± 0.2 months in Iran [24], we are planning to follow the participants for occurrence of planned pregnancy about 18 months after the intervention.

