### Blinding

Given the nature of the intervention, it is not possible to blind participants to researchers involved in providing the intervention and data collection. However, allocation to intervention or control groups will be blinded for researchers in the data set available during the data analysis. To avoid the potential contamination between two groups, we will provide the educational intervention after the typical premarital counselling.

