### Ethical considerations

The ethical approval of the research project was obtained from the ethics committee of National Institute for Medical Research Development (NIMAD) (IR.NIMAD.REC.1399.123). Eligible couples will be invited for an additional counselling by a health provider to ensure that they are entirely informed on the nature of the research by means of oral and written information. All the participants who agree to participate in the study, will sign a written informed consent before the randomization. All participants have the right to withdraw from the study anytime and for any reasons. The educational package will be provided to the control group as well upon their request at the end of the study. To protect against loss of confidentiality, data sheets will be stored on a password-protected computer, which can be accessed only by the members of the research team. Information on participants will be sent to the PI only as de-identified, aggregate data.

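### The retention incentive is reproductive health counselling, offered to both arms and not limited to the last survey; if usable before month 18 it may narrow the 12- and 18-month contrasts

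*Protocol article*

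**What the plan says.** The Data collection section sets the schedule: "Data will be collected by questionnaires at baseline and 3, 12 and 18 months after the intervention in each selected city". To keep participants in follow-up, it offers those eligible an incentive: "A gift voucher for free sexual and reproductive health counselling) on the completion of the survey which may increase response rates". No arm is excluded, no wave is named, and neither the content of the counselling nor a redemption date is given. The next sentence of that section describes reminders to non-respondents.

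Three other sections bear on this:

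- Interventions defines the comparator: "The control group will receive only typical premarital counselling".
- Ethical considerations delays controls' access to the tested material: "The educational package will be provided to the control group as well upon their request at the end of the study".
- Blinding gives the only contamination measure: "To avoid the potential contamination between two groups, we will provide the educational intervention after the typical premarital counselling".

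The Outcomes section lists what could be affected: "The primary outcomes are fertility knowledge, childbearing intention and the first planned pregnancy rate (positive pregnancy test", and "The secondary outcomes include the contraception method use, miscarriage and unplanned pregnancy". Table 1 schedules all of these at 3, 12 and 18 months.

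**The concern.** The incentive is close in subject to the thing being tested. The package described under Interventions covers the fertile window, the effect of age and lifestyle, sexually transmitted disease, delay in childbearing, and the evaluation and treatment of infertility. A session on sexual and reproductive health could plausibly cover some of this, and it could plausibly influence knowledge, intention, contraceptive choice and the timing of a first pregnancy.

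The authors clearly meant to protect the contrast, since they withhold the package from controls and name contamination as a risk. A voucher that can be redeemed during follow-up would work against that intention. It would go to people who complete surveys, who are largely the people supplying the later outcome data. At stake are the 12- and 18-month comparisons, including planned pregnancy, the outcome for which the 18-month follow-up was chosen. If many controls used the voucher, a small or absent difference at those waves would be harder to interpret. Analysis cannot undo counselling that has already been given.

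**Working it through.** **1. When the voucher could matter.** The article names no wave, so each possibility is taken in turn.

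| Voucher earned at | Comparisons it could reach |
|---|---|
| Baseline survey | 3, 12 and 18 months |
| 3-month survey | 12 and 18 months |
| 12-month survey | 18 months |
| 18-month survey only | none |

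The stated purpose is to reduce loss to follow-up, which makes issue at the earlier follow-up surveys plausible, but the text does not settle it. Only the last row fits, without further conditions, both the comparator under Interventions and the delayed access under Ethical considerations.

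**2. Whether the safeguard covers it.** Giving the education after the usual session controls what couples hear on the day of premarital counselling. It has no bearing on a session booked months later.

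**3. The plan's own sample size.** Inputs from Sample size: d = 0.2, α = 0.05 (two-sided reproduces the figure), power 90%, 15% loss.

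- Normal approximation: n = 2(1.96 + 1.2816)² / 0.2² = 525.4, so 526 per group. The t-test solution is 526.3, which rounds up to the stated 527.
- Allowing for loss: 527 / 0.85 = 620 per group, as stated.

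This calculation is tied to knowledge and intention at 3 months. A voucher first issued at the 3-month survey comes too late to affect it.

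**4. What a shared voucher does to a later difference.** Let q_C and q_I be the proportions using the voucher in the control and intervention arms, and g_C and g_I the resulting gains in SD units. The expected difference becomes

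d′ = d − (q_C·g_C − q_I·g_I).

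If both arms use it equally and gain equally, d′ = d and nothing is lost. The contrast narrows only if controls gain more overall. That direction is plausible, because couples already taught the material have less left to learn and the Cardiff scale is a bounded 13-item score. The article gives none of the four quantities.

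**5. Illustrative range (assumptions, not findings).** Suppose d = 0.2 also held at a later wave with 527 analysed per group. Take the extreme case in which a share q of controls gain the full effect and the intervention arm gains nothing, so d′ = 0.2(1 − q).

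Power = Φ(d′·√(527/2) − 1.96), with √(527/2) = 16.233.

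| q | d′ | d′ × 16.233 − 1.96 | Power |
|---|---|---|---|
| 0 | 0.20 | 1.287 | 90% |
| 10% | 0.18 | 0.962 | 83% |
| 20% | 0.16 | 0.637 | 74% |
| 30% | 0.14 | 0.313 | 62% |

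A milder case: with 20% uptake in each arm, g_C = 0.2 and g_I = 0.1, d′ = 0.2 − (0.04 − 0.02) = 0.18, and power is 83% rather than 74%.

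These figures concern a continuous outcome at a later wave. They do not describe the 3-month analysis, and they do not carry over to planned pregnancy, which is a yes/no outcome not sized on d.

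**The case against.** The strongest reply is that the article leaves the voucher's terms open and that a journal article usually does. It refers to a single survey, and a voucher earned at month 18 would harm nothing and would match the plan to give controls the package at study end. The content of the counselling is not stated to be fertility education. All of this stands, and it is why the point is conditional.

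Several stronger readings are tempting, and the document does not support them:

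- A reader might infer that the article flatly contradicts itself. It does so only if the voucher can be used before the final assessment and the counselling overlaps with the package; neither is stated.
- A reader might infer that the voucher must dilute the effect. Both arms receive it, so attenuation depends on controls gaining more than the educated arm.
- A reader might infer that a positive result could not be credited to the package. Couples are randomised and the voucher is offered alike to both arms, so a difference is still caused by allocation, measured against a shared background. If the voucher does narrow the gap, a positive result is conservative.
- A reader might infer that the trial's planned 90% power is lost. That power belongs to the 3-month comparison, which a voucher issued from month 3 cannot reach and which would help in interpreting a later null result.

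The Sample size section also reports that the repeated measures analysis needs only 330 per group, so there may be some margin across waves. It does not give the inputs to that figure, so the margin cannot be turned into a tolerance for dilution.

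What remains is that the plan has chosen an incentive close in subject to the intervention, offers it to controls, and does not confine it to the end of follow-up.

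**Conclusion.** The point holds in conditional form. If the counselling voucher can be redeemed before month 18, it conflicts with a comparator of typical premarital counselling only and with withholding the package until study end, and the stated contamination safeguard does not cover it. It may then attenuate the 12- and 18-month differences in knowledge, intention, contraception use and planned pregnancy. Only a voucher earned at baseline could also reach the 3-month comparison.

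The size cannot be derived from the document, which gives no uptake, content or effect for the voucher. The 83% to 62% range rests on an assumed 10% to 30% dilution, on d = 0.2 holding at later waves, and on no benefit from the voucher in the intervention arm. It shows that an effect this small leaves little room for dilution; it is not an estimate of lost power. The case for acting is that the risk is avoidable at almost no cost beforehand and cannot be repaired afterwards.

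**What to change.** Replace the counselling voucher with an incentive of similar value that has no health-education content, such as phone credit or a shopping voucher. Alternatively, state that the counselling voucher is issued, or can be redeemed, only after the 18-month survey, alongside the package already promised to controls at study end.

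In either case, add one question at 12 and 18 months on other fertility or reproductive health counselling received, and report the answers by arm.

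The cost is a change of voucher type or timing and one questionnaire item. A voucher delayed to month 18 may be a weaker inducement at the earlier waves; a neutral voucher given at each wave avoids that drawback.

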### Sample size

According to our primary outcomes including fertility knowledge and intention toward childbearing that are important to be measured 3 months after the intervention, we considered a small standardized Cohen effect size (d = 0.2) with a type I error of 5% (α = 0.05) and a type II error of 10% (β = 0.1; power = 90%) and sample size obtained 527 in each group and considering 15% of loss to follow up, the sample size was calculated 620 couples in each group using the G-Power software. Considering the design effect equals to 1.5, final size was calculated 1240 couples in total (620 couples in each group). In each city around 200 couples (100 in each group) and from Tehran about 440 couples (220 in each group) will be recruited.

It should be noted that in order to compare quantitative outcomes between groups over time (baseline, 3, 12 and 18 month), the sample size obtained 660 couples in total (330 in each group) based on repeated measures ANOVA. So, the initial obtained sample size (620 couples in each group) will have the appropriate power for this analysis.

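### Pregnancy status, a primary outcome, comes only from a self-completed online form, and the final telephone contact with non-respondents is described as a reminder rather than a chance to collect it

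*Protocol article*

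**What the plan says.** The Outcomes section of the protocol article states: "The primary outcomes are fertility knowledge, childbearing intention and the first planned pregnancy rate (positive pregnancy test"). Under The study instrument, pregnancy, including whether it was planned, is one of the things participants report in the self-administered set. Data collection then fixes the route for follow-up at 3, 12 and 18 months: "The post-test questionnaires will be completed by the participants through online forms". No clinic record, laboratory report or interview is named as another source.

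The retention measures are in the same section. A voucher is offered on completion: "To minimize loss to follow up, we will provide an incentive to the eligible participants". Non-respondents are then chased in steps: "Four reminder emails or text messages will send out to non-respondents at one, two, three, and 4 weeks; a fifth telephone reminder was also undertaken". The sample size allows for attrition, "considering 15% of loss to follow up", which takes 527 per group to 620 couples per group.

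**The concern.** The knowledge scale and the intention questionnaire need the participant to work through items. Pregnancy status does not: it is a short fact about the couple that either partner can give in a minute. The plan already pays for a telephone contact with the couples most at risk of being lost, yet uses that contact only to ask again for the form. Where the form still does not arrive, the primary outcome is missing, and no later analysis can recover a status that was never asked for.

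Non-response may well be related to this outcome. Newly pregnant couples, separated couples and couples putting off childbearing all have reasons not to answer. If the relation differs between arms, the planned-pregnancy comparison is biased. Enlarging the sample for loss protects power but does nothing about this.

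**Working it through.** **Inputs from the protocol article (Sample size):** standardized effect 0.2, type I error 5%, power 90%, 15% loss, 620 couples per group.

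**Step 1: the plan's own figures.** The normal approximation, two-sided, gives n = 2 × (1.960 + 1.282)² / 0.2² ≈ 526 per group; the noncentral t gives 527 (power 0.9004; 526 gives 0.8998). Inflating for loss, 527 / (1 − 0.15) = 620. Both stated figures reproduce.

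**Step 2: size of the planned loss.** 0.15 × 620 = 93 couples per group, 186 in total. With 527 left per group, power for an effect of 0.2 is still 90%. The issue is possible bias, not power.

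**Step 3: what bias could follow.** The article gives no expected pregnancy rate, so everything here is assumed: the true rate p is the same in both arms, a fraction L = 0.15 is lost in each arm, control losses are random, and lost intervention couples have rate q.

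Observed intervention rate = (p − L × q) / (1 − L)

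False difference = (p − q) × L / (1 − L) = 0.1765 × (p − q)

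With p = 50%:

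| Rate in lost intervention couples | Observed intervention rate | Observed control rate | False difference |
|---|---|---|---|
| 40% | (0.50 − 0.15 × 0.40) / 0.85 = 51.8% | 50% | +1.8 points |
| 30% | (0.50 − 0.15 × 0.30) / 0.85 = 53.5% | 50% | +3.5 points |
| 60% | (0.50 − 0.15 × 0.60) / 0.85 = 48.2% | 50% | −1.8 points |
| 70% | (0.50 − 0.15 × 0.70) / 0.85 = 46.5% | 50% | −3.5 points |

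The last two rows show the opposite direction, as when newly pregnant couples are the ones who stop answering. If the lost couples had the same rate in both arms, the false difference under this null would be zero; the bias needs a difference between arms.

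**Step 4: against sampling error.** With 527 per arm and a rate near 50%, the standard error of the difference is √(2 × 0.25 / 527) = 3.08 points. The false differences are therefore 1.76 / 3.08 = 0.57 and 3.53 / 3.08 = 1.15 standard errors. The chance of a two-sided p below 0.05 with no true effect becomes about 9% (upper tail 1 − Φ(1.96 − 0.57) ≈ 0.08, plus a lower tail below 0.01) or about 21% (1 − Φ(1.96 − 1.15) ≈ 0.21), instead of 5%.

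**Step 5: limits of the example.** The 15% is the article's allowance in a calculation that refers to knowledge and intention at 3 months. Applying it to pregnancy at 18 months is a further assumption.

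**The case against.** The case against is substantial. Four staged reminders, a telephone call, a voucher and a 15% allowance form a deliberate retention plan, and nothing in the passage is misstated. Both men and women are recruited, so a couple's status may be lost only if neither partner answers. The pregnancy rates above come from no document, the selective loss is put in by hand, and its direction is unknown. Asking by telephone whether a pregnancy was intended replaces a private answer with one given to staff who, under Blinding, are not blinded, and that distinction defines the outcome.

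Most of this stands as a limit on size and priority. It does not remove the gap: the article does not say that one partner's report suffices, it counts loss in couples, and the call as described collects nothing.

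A reader might also infer that intervention couples who tire of the training will drop out of follow-up, because contact details are requested for both purposes: "will be asked in order to send the post-test questionnaire links and some virtual educational materials". The document does not support that. It collects telephone, email and WhatsApp details and does not say that one sender is used for everything. Training lasts 4 weeks, while the first follow-up form comes 3 months after the intervention. Nor does the withdrawal sentence help that reading: "All participants have the right to withdraw from the study anytime and for any reasons" concerns leaving the study and does not say that stopping the sessions ends the questionnaires. Rules for partial withdrawal are commonly left to the full protocol, so their absence from an article is no finding.

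**Conclusion.** The point holds in a limited form. A primary outcome that could be obtained in a brief conversation rests on online self-completion alone, and the one live contact planned with non-respondents is not used to collect it. The planned loss is 93 couples per arm. Under the stated assumptions the resulting bias is 1.8 to 3.5 points in either direction, roughly half to just over one standard error. These figures illustrate what selective loss could do; they do not predict that it will occur, or in which arm. It would be wrong to conclude that non-respondents are barely pursued, or that leaving the training means leaving follow-up. This is a worthwhile, inexpensive improvement to data collection, not an error that undermines the trial.

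**What to change.** In both arms, make the fifth contact a fixed-script minimum-data call for those who have still not completed the form. Four items suffice: pregnancy since the last wave (yes or no), date of the first positive test, whether it was intended, and any miscarriage. Accept the answers from either partner and record the mode of collection. Add a sensitivity analysis of planned pregnancy restricted to online reports, so that any effect of mode can be seen.

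The cost is a short script and a mode variable; the call itself is already planned. The downside is that some outcomes, above all the planned or unplanned classification, will be given by voice to an unblinded caller. Fixed wording, identical use in both arms and the restricted analysis limit that risk but do not remove it.

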### The study instrument

Participants will respond to a self-administered demographic characteristics questionnaire, the Cardiff Fertility Knowledge Scale (CFKS), the childbearing intention questionnaire and some questions about their pregnancy (planned/unplanned pregnancy).

